### Blinding

After the number assignment, (i) the research team will blindly provide “Walk@Work-App Kits” for each patient corresponding to either the control or intervention group to nurses. Both kits will have the same look (Fig. 2) but with different content depending on whether the patient belongs to the intervention or control group (Fig. 3). The physician, in charge of recording and monitoring clinical data, will be blinded to the patients’ group randomization. Patients will be blinded to the existence of other patients receiving the intervention or being in a control group. The independent researcher who evaluates the participants at the end of the intervention and at the 6- and 12-month follow-ups will be blinded to the participants’ treatment group assignment. In addition, the person who will carry out the data analysis will not participate in the data collection.

**Fig. 2 Fig2:**
[figure not shown]
Walk@Work-AppKits provided to nurses of primary health care centres

**Fig. 3 Fig3:**
[figure not shown]
Content of the control (a) and intervention (b) groups kit for Walk@Wor-kApp program

### Intervention

The Walk@Work-Application (W@W-App) is an automated mobile phone and web-based intervention that focuses on decreasing and breaking up prolonged occupational sitting time in desk-based office employees. The W@W-App includes a self-monitoring tool that adds a commercially available sensor (MetaWearC; MbientLab Inc) [62] covered with a waterproof round case and attached via a band to the thigh. The sensor gathers employee’s postural and movement information during working hours. The W@W-App communicates with the MetaWearC external sensor by synchronizing the raw sensor data with the W@W-App software via a low-energy Bluetooth System. Postural and movement data are directly processed and displayed in real time by the app on the phone. Figure 4 depicts the W@W-App (login page) and the MetaWearC sensor.

**Fig. 4 Fig4:**
[figure not shown]
(a) Walk@Work-App interface; (b) the MetaWearC sensor with the case and thigh band

The W@W-App+MetaWearC was developed from a previous version [63] to self-monitor and quantify occupational sitting, standing and stepping while offering real-time feedback on these behaviours (Fig. 5). Both are essential components for changing behaviours at the time and place where they occur, as well as for increasing individuals´ awareness and empowerment toward behaviour change [64]. The W@W-App+MetaWearC self-monitoring system has demonstrated a high level of accuracy and validity in determining postural position, providing a low-cost alternative tool for the examination of occupational sitting, standing, stationary and upright times in desk-based office employees [65].

**Fig. 5 Fig5:**
[figure not shown]
Walk@Work-App interface displaying employees’ occupational stepping, sitting and standing time

#### Walk@Work-App registration, configuration and instalment

Participants will install and configure the W@W-App, following the guidance provided: (i) registration on the W@W web platform (http://walkatwork.uvic.cat/en/) [66]; (ii) user verification through email; (iii) W@W-App installation and initialization; (iv) recording day and time period configuration (i.e. between 3 and 8 working hours); and (v) recognition of the MetaWearC sensor via Bluetooth. Participants can also read the private policy of the W@W-App on the W@W website. Registration and employee guidance is available on a YouTube tutorial at https://youtu.be/cS0oJ9xPTbo. The W@W-App is available for downloading in Google Play and App Store. After registration and configuration, the complete W@W-App will be installed on the employees´ own mobile phones for 13 weeks, the period during which employees will wear the band with the attached MetaWearC, only during working hours (including the time taken to go to and back from work).

*Description of how the W@W-App programme for changing occupational sedentary time works.*

During Week 0, the W@W-App provides self-monitoring features to get baseline measurements for occupational stepping, sitting and standing time and set up a programme baseline with individual targets for each employee. During Weeks 1–12, the app keeps self-monitoring and displaying employees’ occupational activity in real-time, including an emoji of an animated chair at the bottom of the screen. According to the time spent in sitting bouts, the chair changes from a green chair (< 20 min) to a yellow chair (20–40 min) and then to a red chair (40–60 min) (Fig. 6). When sitting time is prolonged for more than one hour, a vibration feature of the mobile phone is activated.

**Fig. 6 Fig6:**
[figure not shown]
Chair images with feedback displayed on the Walk@Work-App mobile screen

At the end of the working day, the mobile application sends data to the web server and it returns a daily summary message with the support of a chair image reflecting how well the employee has done in reaching the previously set-up individualized goals. In this message, participants can see the chair that represents their daily goals achievement (Fig. 7).

**Fig. 7 Fig7:**
[figure not shown]
Chair images with feedback on employees’ summary of daily activity displayed on Walk@Work-App

When one or both targets have been achieved during most days of the week, a congratulations message is sent at the end of the working week with the support of a blue chair image. These weekly motivational messages report the progress made, appearing only when the goals are completed. Additionally, daily graphs provide feedback on employees´ occupational sitting and moving time (Fig. 8). While in the App these graphs can be checked weekly, in the W@W-App website (Fig. 9) the graphs show continuous feedback from week 0 to week 12 in relation to the goals that should be achieved throughout the programme.

**Fig. 8 Fig8:**
[figure not shown]
Graphs with employees’ feedback on sitting and moving time displayed on W@W-App mobile screen

**Fig. 9 Fig9:**
[figure not shown]
Graphs with employees’ feedback on sitting and moving time displayed on W@W-App website

Most importantly, during Weeks 1–12 employees have access to automated strategies to sit less and move more at work during an 8-week ramping phase and a 4-week maintenance phase. During this period, fortnight and weekly messages inform employees about the strategies and goals that can be used to change their occupational sedentary behaviour. During the ramping phase, every two weeks employees are challenged to progressively increase their movement by replacing occupational sitting time with 10 minutes (Weeks 1–2), 20 minutes (Weeks 3–4), 30 minutes (Weeks 5–6) or 37 minutes (Weeks 7–8) of moving or stepping above the average baseline (Week 0).

#### Description of the W@W-App strategies

Strategies to achieve the programme goals initially focus on reducing and breaking occupational sitting time by performing work tasks actively, such as active email, breaking up meetings time, getting off the chair briefly to move the joints, walking while talking on the phone and getting up to throw documents in the trash, drink water or print documents (Weeks 1–2). These progress to include short 5-minute walks, for example active parking, active relaxation at work, holding meetings while walking with one or two people or using the farthest bathroom (Weeks 3–4) and then longer walks of 10 minutes by targeting active transport, active breakfasts or including walks in the itinerary to get to work and back home (Weeks 5–6). During weeks 7–8, workers are encouraged to walk with greater intensity by using the stairs, walking briskly or adding three periods of 5–10 minutes of walking per day. Additionally, employees are encouraged to check resources on Twitter that explain in detail the benefits of replacing sitting time for light or moderate physical activity, share with users the barriers they find to reducing sitting time during the work day and show solutions to overcome these barriers. Finally, employees are encouraged to find their own strategies to sit less and move more at work and share them in the W@W-App Twitter. Over these 8 weeks, employees are also encouraged to share their active work experiences on the W@W-App Twitter and share the 5 to 10-minute walks added to their work routine to help others discover various routes and times to walk at work.

During the maintenance phase (weeks 9–12), employees are challenged to keep reducing daily sitting time and increase movement or walking time by 40–60 minutes a day. Strategies to achieve this goal focus on reducing sitting time at weekends, adding commuting or walks in the employees´ immediate environment where they live or work, staying active by helping others and being active or sharing knowledge with others about the benefits experienced from sitting less and being more active. The W@W-App strategies and intervention have been developed from previous versions [67, 68].

#### Description of the W@W-App behaviour change techniques

W@W-App provides a range of effective behaviour change techniques to reduce and break up sitting time and increase physical activity at work [69]. Underpinned by the Behaviour Change Wheel, a theoretically driven framework that incorporates multiple theories of behaviour change [70], the behaviour change techniques included in W@W-App are: (i) Feedback on behaviour and outcomes of behaviour (e.g. providing real-time feedback on the behaviours at the time when they occur); (ii) Self-monitoring of behaviour and outcomes of behaviour (e.g. providing graphics and messages with individual feedback on progress); (iii) Information about health consequences (e.g. providing articles on the health benefits of replacing sitting time with physical activity); (iv) Goal setting (i.e. setting goals every 2 weeks for reducing occupational sitting time and increasing moving); (v) Action Planning (e.g. providing groups of strategies that are progressively planned to increasing the length of the breaks in sitting time); (vi) Social support (i.e. providing a social network for sharing experiences and strategies using twitter or the blog); (vii) Instructions on how to perform the behaviour (e.g. providing detailed instructions of the tasks that can be done to reduce occupational sitting); and (H) Prompts (e.g. using coloured chairs).

### Outcomes

The following outcomes will be assessed on the effectiveness of W@W-App: (i) Objective and subjective habitual and occupational sedentary behaviour, measured by the activPAL3TM device (PAL Technologies Ltd., Glasgow) and the Workforce Sitting Questionnaire (WSQ) [71, 72]; (ii) Objective and subjective habitual and occupational physical activity, measured with the activPAL3TM device and the Spanish Brief Physical Activity Assessment Tool (SBPAAT) [73, 74]; (iii) Glycaemic control variables using glucose, glycosylated haemoglobin A1c (HbA1c); (iv) Anthropometric variables by weight, height, body mass index (BMI), and waist circumference; (v) Lipid profile by total cholesterol, high-density lipoprotein (HDL) and low-density lipoprotein (LDL) and triglycerides; (vi) Systolic and diastolic blood pressure (BP); (vii) Mental well-being measured with the Warwick-Edinburgh Mental Well-being Scale (WEMWS) [75]; and (viii) Work-related outcomes including presenteeism measured with the Work Limitations Questionnaire (WLQ) [76], sickness absence [77], work-related stress (Job Content Questionnaire, JCQ) [78] and impact of work on employees’ health [77].

#### Subjective habitual and occupational sedentary behaviour and physical activity

A seven-day total and domain-specific sitting time questionnaire (Workforce Sitting Questionnaire, WSQ) will assess weekly sitting time (minutes/day) at work *and* while travelling to and from work [71]. These domains will be targeted since Walk@Work-App aims to reduce sitting time (i) at work and (ii) while commuting. This questionnaire has high validity and reliability in the adult population for weekday sitting time at work (r = 0.69–0.74), while it is lower for weekend days across all domains (r = 0.23–0.74) [78]. Forward-backward translation into Catalan and Spanish identified linguistic equivalence [79]. The Spanish version of a Brief Physical Activity Assessment Tool (SBPAAT) will identify participants who are insufficiently active versus those who follow the health recommendations for physical activity [73]. The SBPAAT has showed moderate validity (k = 0.454, 95% CI: 0.402–0.505) and a specificity and sensitivity of 74.3 and 74.6%, respectively. Validity is fair for identifying daily minutes engaged in moderate (r = 0.215, 95% CI: 0.156 to 0.272) and vigorous PA (r = 0.282, 95% CI: 0.165 to 0.391) [73].

### Objective habitual and occupational physical activity

The activPAL3TM will be used to measure and quantify the sedentary behaviour patterns and physical activity of employees across weekdays (working and non-working time) and weekends. Working and non-working times will be established by using participants’ daily records. The activPAL3TM device is a valid measure to quantify body posture and activity patterns during free-living conditions [72]. The device will be attached to participants’ right thigh using a flexible nitrile sleeve and a transparent film (10 × 10 cm of hypoallergenic Tegaderm™ Foam Adhesive Dressing). The waterproof dressing of the activPAL3TM allows participants to wear the monitor continuously for 24 hours per day for 7 complete days. Participants will receive additional dressings and instructions on how to reattach the device if needed. Additionally, participants will be asked to record their daily wake-up time, bedtime, working hours, and any monitor removal time.

Data will be processed using activPAL Professional Software™ (version 7.2.32), Microsoft Excel 2010 (Redmond, WA, USA), and MATLAB v8.4 (MathWorks®, Natick, MA, USA), following previously published protocols [80]. Resulting from the activPAL3TM software output, the following outcomes will be determined: total sitting time, total standing time, total number of sitting bouts and number of sitting bouts with three different lengths (< 20 min, 20–40 min, 40–60 min and > 60 min). Additionally, total time spent in light-intensity physical activity and moderate-to-vigorous physical activity will be determined by using previously validated count-to-activity thresholds [81].

*Positive mental well-being.*

The Warwick-Edinburgh Mental Wellbeing Scale (WEMWBS) will assess positive mental well-being over the previous 2 weeks [75]. The 14-item scale has five response categories: 1 (“None”) to 5 (“All the time”). Responses are added to identify the final score, 14–70, and indicating low to high positive mental well-being. WEMWBS shows high internal reliability (Cronbach’s alpha = 0.93) and 1 week test-retest reliability (r = 0.97) in the Spanish population [82].

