Although there is no international consensus with regards to healthy sedentary behaviour thresholds for adults, a meta-analysis suggested that adults’ sedentary time should be limited to 7-8 h/day [4]. Other public health guidelines also recommend breaking up sedentary behaviour every 30 minutes [32]. And the World Health Organization (WHO, 2020) [20] suggests that adults should limit the amount of time they spend sedentary.

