### Data collection methods

The data collection will be carried out at the beginning and at 3, 6 and 12 months using the activPAL3TM device, data from the computerized medical history and a survey. At 6 and 12 months, each patient will have a blood test done for the clinical variables (Table 1). In each measurement, the participants will be summoned in consultation to record the subjective and objective habitual and occupational sedentary behaviour and the subjective and objective habitual and occupational level of physical activity.

**Table 1 Tab1:** Data collection methods for the Walk@Work-App study protocol of a randomized controlled trial

	Variables	Baseline	Follow-up			Variable type	Objective
		**t = 0** **Months**	**t = 3 Months**	**t = 6 Months**	**t = 12 Months**		
**PARTICIPANT CHARACTERTISTICS**	Socio-labour level	X				QV	Factors that can affect the final result
	Number of working hours	X				CV	
	Changes in glucose-lowering dose within last 3 months		X	X	X	QV	
	Antidiabetic drugs or insulin	X	X	X	X	QV	
	Type of insulin	X	X	X	X	QV	
	Diet	X	X	X	X	QV	
	Change in diet		X	X	X	QV	
**HABITUAL AND OCUPATIONAL SEDENTARY BEHAVIOUR AND PHYSICAL ACTIVITY**	Total sitting time, workday, weekend (ActivPAL3TM)	X	X	X	X	CV	Reduce
	Number of sitting time interruptions workdays, weekend (ActivPAL3TM)	X	X	X	X	CV	Increase
	Sedentary bouts < 20 minutes workdays, weekend (ActivPAL3TM)	X	X	X	X	CV	Reduce long periods of sitting/ increase short periods of sitting
	Sedentary bouts 20–40 minutes workdays, weekend (ActivPAL3TM)	X	X	X	X	CV	
	Sedentary bouts 40–60 minutes workdays, weekend (ActivPAL3TM)	X	X	X	X	CV	
	Sedentary bouts > 60 minutes workdays, weekend (ActivPAL3TM)	X	X	X	X	CV	
	Standing time workdays, weekend (ActivPAL3TM)	X	X	X	X	CV	Reduce
	Activity time workdays, weekend (ActivPAL3TM)	X	X	X	X	CV	Increase
	Light-intensity physical activity workday, weekend (ActivPAL3TM)	X	X	X	X	CV	Increase
	Moderate-to-vigorous physical activity workday, weekend (ActivPAL3TM)	X	X	X	X	CV	Increase
	Sufficiently or insufficiently active (SBPAAT)	X	X	X	X	CV	Increase
	Domain-specific sedentary behaviour (WSQ)	X	X	X	X	CV	Reduce
	Glycaemic index (mg/dl)	X		X	X	CV	Reduce
	HbA1C (%)	X		X	X	CV	Reduce
**LIPID PROFILE**	Total Cholesterol (mg/dl)	X		X	X	CV	Reduce
	HDL (mg/dl)	X		X	X	CV	Increase
	LDL (mg/dl)	X		X	X	CV	Reduce
	Triglycerides (mg/dl)	X		X	X	CV	Reduce
**ANTHROPOMETRIICS**	Weight (Kg)	X	X	X	X	CV	Reduce
	Height (cm)	X	X	X	X	CV	–
	BMI (kg/m^2^)	X	X	X	X	CV	Reduce

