### Statistical methods

A descriptive study of all the measured variables will contain the mean, standard deviation, minimum and maximum value and dispersion coefficient. The homogeneity of the intervention and control group at the initial moment – that is, that there are no statistically significant differences between the two groups in any of the variables measured – will be verified by performing a two-tailed test of means for independent samples for each variable (Additional file 2).

The effect of the mHealth W@W-App programme will be measured by continuous variables (Table 1) which will be used to evaluate the differences between before and after implementing the mHealth programme. In some variables, the programme will be effective if the mean increases in the intervention group while for other variables effectiveness will happen if the mean decreases. For example, the programme will be effective if physical activity increases and total cholesterol decreases. Therefore a one-tailed test of means will be performed. For these continuous variables, the difference of the variable between moment t of the measurement and the initial moment will be calculated, (*X*_*Dt*_ = *X*_*t*_ − *X*_0_), which quantifies whether there have been changes, after t months, associated with the intervention. The intervention has a positive effect if the results of the intervention group are significantly better than those of the control group; that is, if the values of the variable *X*_*Dt*_ are better in the intervention group. The qualitative variables (see Table 1) will be used to check if any patients display unusual behaviour that are due to changes in their medication or diet [86]. Intention-to treat analysis will be used. The statistical tests to be carried out in the event that homogeneity between the groups is not accepted while the procedure is outlined in Additional file 3.

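### Counts of sitting bouts per length class have no single favourable direction, yet they are effectiveness outcomes under one-tailed tests

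*Protocol article*

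**What the plan says.** The section on objective habitual and occupational physical activity (Protocol article) derives several outcomes from the activPAL output. They include "total sitting time, total standing time, total number of sitting bouts" and the "number of sitting bouts with three different lengths (< 20 min, 20–40 min, 40–60 min and > 60 min". The text says three classes but names four.

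Table 1 lists the four classes as continuous variables for workdays and weekends. They share one objective: "Reduce long periods of sitting/ increase short periods of sitting". It does not say whether 20–40 and 40–60 min count as long or short. A separate row, "Number of sitting time interruptions workdays, weekend (ActivPAL3TM", has the objective of an increase.

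The Statistical methods compare change from baseline between arms for each continuous variable. Because benefit means a rise in some variables and a fall in others, the section concludes: "Therefore a one-tailed test of means will be performed".

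The app uses the same cut-points for its cues: "the chair changes from a green chair (< 20 min) to a yellow chair (20–40 min) and then to a red chair (40–60 min". It then adds: "When sitting time is prolonged for more than one hour, a vibration feature of the mobile phone is activated". The Background reports that "Other public health guidelines also recommend breaking up sedentary behaviour every 30 minutes".

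**The concern.** A one-tailed test needs a favourable direction that is fixed in advance and that really tracks benefit. A count per length class does not supply one. Breaking a bout removes it from its class and puts its pieces into the same or lower classes. A middle class can therefore gain from above and lose to below at the same time, and its net change says little about whether sitting was broken up. For 20–40 and 40–60 min the article prints no direction at all. For > 60 min the intended direction is clear enough, but the count can move against it when a very long bout is broken late.

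Breaking up prolonged occupational sitting is what the app is built to do, and sedentary behaviour is the main objective. The four class results could contradict one another with no stated rule for reading them. A one-tailed test pointed the wrong way could not register a real change.

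**Working it through.** The plan gives no figure for these outcomes, so there is none to reproduce. The check reclassifies bouts by arithmetic.

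**Inputs from the article:** class cuts at 20, 40 and 60 min, and a vibration after more than 60 min of sitting. **Assumptions for illustration:** the starting bout lengths; the break points (61 min for standing just after the prompt, 59 min for standing just before it, and earlier breaks); and total sitting time held fixed.

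**Rule:** replace a bout of L minutes by pieces that sum to L, then count pieces per class and add up the minutes in pieces above a threshold.

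| Start | Pieces | < 20 | 20–40 | 40–60 | > 60 | Min in bouts > 60 | Min in bouts > 30 |
|---|---|---|---|---|---|---|---|
| 30 | 15 + 15 | 0→2 | 1→0 | 0→0 | 0→0 | 0→0 | 0→0 |
| 50 | 30 + 20 | 0→0 | 0→2 | 1→0 | 0→0 | 0→0 | 50→0 |
| 110 | 59 + 51 | 0→0 | 0→0 | 0→2 | 1→0 | 110→0 | 110→110 |
| 4 × 90 | 4 × (61 + 29) | 0→0 | 0→4 | 0→0 | 4→4 | 360→244 | 360→244 |
| 180 | 61 + 61 + 58 | 0→0 | 0→0 | 0→1 | 1→2 | 180→122 | 180→180 |

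Every row is an improvement in the sense of Table 1, because sitting is interrupted more often.

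- The 20–40 min count falls in the first row and rises in the second and fourth.
- The 40–60 min count falls in the second row and rises in the third and fifth.
- The > 60 min count falls in the third row, is unchanged in the fourth and rises in the fifth.

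**How general the last result is.** Take single bouts of 62 to 240 min in 1-min steps (179 lengths), each broken at every 61 min. The > 60 min count falls in 0, is unchanged in 60 (62–121 min) and rises in 119 (122–240 min). The 40–60 min count rises in 60 of the 179. These are shares of hypothetical lengths, not frequencies in patients.

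**Why minutes behave better.** If a bout of length L exceeds threshold c, its pieces above c sum to at most L. If L does not exceed c, no piece does. Splitting at fixed sitting time therefore can never increase minutes in bouts above c. Both minutes columns show this: they fall or stay level, never rise.

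**Whether the companion outcomes fill the gap.** Compare 8 bouts of 29 min with 4 of 37 plus 4 of 21 min. Both total 232 min (8 × 29 = 232; 148 + 84 = 232), both have 8 bouts, and all 8 fall in the 20–40 min class. Yet 0 bouts exceed 30 min in the first pattern and 4 in the second. Total sitting, number of bouts and class counts cannot separate the two.

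**The case against.** The best case for the plan has four parts.

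- **The cut-points have a reason.** They match the app's colour cues, so the classes describe the behaviour the app gives feedback on. That stands, and it supports keeping the counts as description.
- **The shared objective can be read as a redistribution** from long to short bouts, not as four separate verdicts. That is a fair reading of Table 1. But the Statistical methods test continuous variables by a difference in means in one direction, and no joint test of a redistribution is described. A rule may stand in the additional files or an analysis plan, which are not shown. Even so, a stated direction for a middle class would not make its count track benefit.
- **Other outcomes capture breaking up.** In the 180-min example the number of bouts rises from 1 to 3, which correctly shows improvement. So sitting pattern is not scored by class counts alone. None of the companions, however, measures the length of uninterrupted sitting. Total time divided by number of bouts would give only a mean, and it is not listed.
- **The examples hold sitting time fixed**, whereas the programme also replaces sitting with movement. This is true. The examples isolate the effect of breaking bouts and do not predict the trial's result.

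Two stronger readings are tempting, and the article does not support them. A reader might infer that a patient who obeys the 60-min prompt thereby produces 40–60 min bouts. But the phone vibrates only after more than an hour, so the interrupted bout is already in the > 60 min class. Four 90-min bouts become 61 + 29 each, and the 40–60 min count stays at 0. Such bouts arise only from the remainder or from standing before the prompt. A reader might also infer that the 30-min interval cannot be assessed at all. It is background guidance, not a target or outcome of this trial, and the limit applies to the listed outcomes. Nothing in the article says the device data could not yield another cut-point.

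**Conclusion.** The concern holds as a defect of outcome definition. The 20–40 and 40–60 min counts have no stated favourable direction and can rise or fall when sitting is broken up. The > 60 min count can stay the same or rise when a very long bout is broken just after the prompt (1 to 2 in the 180-min example, while minutes in such bouts fall by 58, from 180 to 122). One-tailed tests on these counts are therefore not well founded.

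The conclusion rests on the class cuts and one-tailed testing as printed, and on illustrative bouts at fixed sitting time. How often the counts would mislead in practice depends on the patients' bout lengths, which the article does not give. Total sitting time and the interruption outcomes are unaffected. The announcement of three classes before a list of four is a separate wording slip.

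**What to change.** - In the outcome section and Table 1, make minutes per day accumulated in sitting bouts longer than 60 min the tested prolonged-sitting outcome, for workdays and weekends, with the objective to reduce.
- If the guideline cited in the Background is to be addressed, add minutes per day in bouts longer than 30 min, also to be reduced.
- Keep the four class counts as description only, without one-tailed tests.
- Correct three to four in the outcome text.

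The cost is small: a short addition to the activPAL processing and some Table 1 wording. No new data are needed, because sorting bouts by length already requires each bout's duration. The downside is that the class counts are no longer tested one by one.
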